### Trial design {8}

This is an interventional, parallel assignment, two-arm, cluster randomized trial. The classes of students will be randomized into a psychoeducational intervention (experimental group) or control condition (control group). All participants will be assessed at baseline, post-intervention, and at the 3- and 6-month follow-up points by using self-report questionnaires. In addition, salivary samples will be collected at baseline and post-intervention. Details on the timeline and assessments are reported in Table 1.

**Table 1 Tab1:**
[figure not shown]
Timeline and assessments of the study

*CIB* Checklist of Impulsive Behaviors, *DBT-WCCL* DBT-Ways of Coping Checklist (DBT-WCCL), *SPSI-R:SF* Social Problem-Solving Inventory-Revised Short Form, *DERS* Difficulties in Emotion Regulation Scale, *PHQ-9* Patient Health Questionnaire, *SCARED* Screen for Child Anxiety Related Emotional Disorders, *PID5* Personality Inventory for DSM-5, *BIS-Brief* Barratt Impulsiveness Scale–Brief, *CTQ* Childhood Trauma Questionnaire, *ASQ* Adolescent Stress Questionnaire, *SCM* School Climate Measure, *CASS* Child and Adolescent Social Support Scale, *FAD* Family Assessment Device

The present study protocol was written in accordance with the Standard Protocol Items: Recommendations for Interventional Trials (SPIRIT) [42].

## Methods: participants, interventions, and outcomes

### Study setting {9}

A total of 20 school classes will be recruited among the high schools of Brescia (Northern Italy), for a total of approximately 440–460 students (considering approximately 22–23 students per school class) attending several high schools in the city. Each school will enroll an even number of classes to be randomized to the experimental or control conditions.

### Eligibility criteria {10}

The inclusion criteria will be as follows: 16–19 years; attending the third year of high school (10th grade); and signing an informed consent form. Exclusion criteria will be a certified diagnosis of learning difficulties or of autism spectrum disorders. All students completed the assessment questionnaires and participated in the project activities.

### Who will take informed consent? {26a}

Participation in the study will be voluntary, and the participants will be allowed to withdraw at any time. Teachers and project staff members will organize meetings with parents and students to introduce the study and to answer their questions. Project staff members will ask both students and parents to sign the informed consent form. Information sheets and consent forms (both for parents and students) were approved by the local ethics committee, the Comitato Etico IRCCS Fatebenefratelli.

### Additional consent provisions for collection and use of participant data and biological specimens {26b}

This trial involves collecting biological specimens of saliva to measure stress and inflammation. On the consent form, participants will be asked to state if they agree to this part of the trial or if they prefer to withdraw from it. As for the other parts of the trial, the subjects will be informed that they can withdraw at any time. In this case, biological samples will be destroyed.

## Interventions

### Explanation for the choice of comparators {6b}

All activities of the trial, both the assessments and the intervention, will be done during school time instead of the usual schooling curricula. Hence, the classes randomized to the control condition will follow their usual schooling curricula and will receive the intervention after the follow-up. All this information is reported in the consent forms. The reasons for our choice are based on the consideration that we did not find an intervention to be as effective as a standard. Moreover, the results of our trial will be useful to support the inclusion of specific curricula in school scheduling, as they are still lacking in our country.

### Intervention description {11a}

The psychoeducational intervention will be based on DBT Skills Training for Emotional Problem Solving for Adolescents (DBT STEPS-A), a manualized program designed to help adolescent students develop coping strategies and decision-making abilities, especially under emotional distress [43]. The DBT STEPS-A covers all four primary skills modules of the DBT skills training (mindfulness, distress tolerance, emotional regulation, and interpersonal effectiveness). The DBT STEPS-A program was created in the US context to be delivered as a universal social–emotional learning curriculum; it consists of approximately 30 weekly lessons organized into 50-min blocks.

For the present trial, we selected within the original DBT STEPS-A the specific elements related to ED. The intervention will consist of four sessions of 2 h each per month (for a total of 8 h) scheduled during regular school time. The details of each session are reported in Table 2. Sessions will be conducted by two psychotherapists (a leader and a co-leader) who have attended specific trainings on DBT [20] and DBT-A [44].

**Table 2 Tab2:** Description of the intervention

	Aims	Contents and skills	Methods^a^
Session 1 (2 h)	1) To describe goals of emotional regulation and function of emotions 2) To enhance emotional literacy	• Emotional dysregulation and emotional regulation skills. • Levels of emotion chart • The concept of biological vulnerability • The functions of emotions • Homework: to describe emotional events through the ABC (Antecedents, Beliefs, Consequences) diary.	- Slideshow - Handouts 15.1, 15.3 - Class exercices
Session 2 (2 h)	1) To practice with the model of emotions 2) To gain the skills to manage interpretations and impulses to action.	• The model of emotions: emotion is a complex response made up of different components (prompting event, interpretation, biological changes, expressions, and aftereffects). • Emotion are set off by our interpretation, not by the events themselves: the skill “Check the facts” • Emotion have an action urge, by changing behavior, we can change emotion: the skill “Opposite action” • Homework: practice with check the facts and opposite action	- Slideshow - Role-playing - Handouts 16.1-2, 17.2-4 - Class exercises
Session 3 (2 h)	1) To improve strategies to solve a problem 2) To learn how to accumulate positive emotions.	• How to solve a problem: the seven steps of problem-solving • Accumulate positive experiences in the short term: the skills “pleasant activities” and “building mastery”. • Accumulate positive experiences in the long term: identifying personal values and plan goals. • Vulnerability factors and the PLEASE skills • Homework: practice with AB Please	- Slideshow - Handouts 18.1, 19.2-5, 20.1-4 - exercises in small groups
Session 4 (2 h)	1) To learn how to reduce intense emotion quickly in order to avoid impulsivity	• The autonomic nervous system and the “fight-or-flight” reaction • Activate parasympathetic system by reducing body temperature, using intense exercise, and engaging in paced breathing: the TIPP skills. • Homework: practice with TIPP skills	- Slideshow - Handouts 6.2, 8.1. - Classes exercices.

^a^The handouts were taken from the Italian version of DBT STEPS-A 44

Active participation of students will be encouraged, and at the end of each session, the key concepts will be written on a poster hanging in the classroom as a reminder. Homework will also be assigned for students to practice the learned skills in a real environment and will be reviewed at the beginning of the following session.

### Criteria for discontinuing or modifying allocated interventions {11b}

There will be no special criteria for discontinuing or modifying the allocated intervention.

### Strategies to improve adherence to interventions {11c}

All activities of the study will be scheduled during regular school time according to academic planning to facilitate students’ attendance.

The contents of the psychoeducational intervention will be structured. The fidelity to the intervention will be supported by regular meetings of the project team. Team meetings will be scheduled weekly during the pre-study phase and will then be scheduled monthly. For each session of the psychoeducational intervention, the co-leader will fulfill a checklist to register the content of the session and to record students’ attendance.

Adherence to the procedure for salivary sample collection will be promoted by phone alert messages at established hours and by written reminders about the exact procedure.

### Relevant concomitant care permitted or prohibited during the trial {11d}

Concomitant care will be permitted.

### Provisions for post-trial care {30}

There is no anticipated harm or compensation for trial participation.

### Outcomes {12}

#### Primary outcomes

##### Emotional regulation skills

DBT-Ways of Coping Checklist (DBT-WCCL) [45]

The DBT-WCCL is a 59-item self-report questionnaire measuring the frequency of DBT skills use (DBT Skills Subscale, 38 items) and dysfunctional coping strategies (Dysfunctional Coping Subscale, 21 items). Participants will be asked to indicate, on a 4-point Likert scale, the frequency of use of each skill in the previous month (i.e., never used, rarely used, sometimes used, or regularly used). The scale showed good internal consistency (Cronbach’s alpha coefficients for the subscales ranged from .84 to .96) and content validity [45]. For our primary outcome analysis, we will assess the difference between the two groups in terms of the proportion of participants categorized as “improved” post-intervention. Specifically, we will consider as “improved” those participants with a difference of at least one category, toward improvement, from the baseline to post-intervention in the frequency of use of functional skills. Intervention efficacy will be defined by a difference of at least 20% (i.e., 12/59 items) of improvement between groups after the intervention.

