##### Impulsive behaviors

Checklist for Impulsive Behaviors (CIB)

This CIB is an ad hoc 15-item checklist created to determine the frequency of impulsive behaviors: alcohol use (4 items), substance use (2 items), internet addiction (4 items), gambling (1 item), non-suicidal self-injury (2 items), unprotected sex (1 item), and binge eating (1 item). Participants will be asked to indicate, on a 5-point Likert scale, the frequency of impulsive behaviors that occurred in the previous month (never; only once a week; two or three times a week; at least 4 times a week). Moreover, the checklist includes a section to evaluate the lifetime frequency of each behavior on a 6-point Likert sale (1–2 times, 3–5 times, 6–9 times, 10–19 times, 20–39 times, at least 40 times). For our primary outcome analysis, we will assess the difference between the two groups in the proportion of participants categorized as “improved” at post-intervention. Specifically, we will consider as “improved” those participants with a difference of at least one category toward improvement from baseline to post-intervention in the frequency of impulsive behaviors. Intervention efficacy will be established by treatment success, defined as at least 13% (i.e., 2/15 item) between groups after the intervention.

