### Sample size {14}

The primary outcome measures will be represented by changes in impulsive behaviors (established by the Checklist for Impulsive Behaviors) and by changes in emotional regulation skills (determined by the DBT-Ways of Coping Checklist).

Precisely, the outcome will be evaluated in terms of change (pre/post) in percentage of “yes” answers in the two groups (treated and control), where “yes” is defined as a difference of at least one category toward improvement from baseline. More specifically, the scores of the Checklist for Impulsive Behaviors are measured on a Likert scale. Therefore, a “yes” answer implies a decrease in the frequency of impulsive behavior; for example, from the category “two or three times a week” to the category “one time a week.” In a similar manner, a “yes” answer for the DBT-Ways of Coping Checklist means a decrease in the use of dysfunctional skills; for example, from the category “regularly used” to “sometimes used,” or vice versa for functional skills.

We assumed that at baseline, there would be a between-group difference by chance of 7% (i.e., 1/15 yes answers, where 15 is the total number of checklist items) on the Checklist for Impulsive Behaviors and that this difference would increase by up to 13% (i.e., 2/15 yes answers) after the intervention. Based on these assumptions and applying a two-sided test for paired binomial proportions, with a significance level equal to 0.05 and a power of 0.8, the estimated sample size was *n* = 340 (170 per group). Moreover, considering a drop-out rate of 20%, the minimum sample size (MSS) reached *n* = 426 (213 per group).

In the same way, we assumed that on the DBT-Ways of Coping Checklist, there would be a difference by chance of 7% (i.e., 4/59 yes answers, where 59 is the total number of the checklist DBT items) at baseline, and that this difference would increase by up to 20% (i.e., 12/59 yes answers) after the intervention. This last hypothesis was made considering that, given the focus of treatment, we expected a greater change in emotional regulation skills than in dysfunctional behaviors. Based on these considerations and applying a two-sided test for paired binomial proportions, with a significance level equal to 0.05 and a power of 0.8, we reached an estimated sample size of *n* = 84 (42 per group).

In sum, due to both the outcome measures and related sample size estimations, the final sample size needed was 426 students.

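### Both primary endpoints count improved students, but no rule turns item categories into an improved student, and the thresholds and sample size are fractions of items

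*Protocol article*

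**What the plan says.** In the protocol article, Outcomes {12}, both primary outcomes are compared between groups as proportions of participants who are improved after the intervention. For the DBT-WCCL, the improved are "those participants with a difference of at least one category, toward improvement, from the baseline to post-intervention in the frequency of use of functional skills". For the CIB, they are "those participants with a difference of at least one category toward improvement from baseline to post-intervention in the frequency of impulsive behaviors".

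The functional part of the DBT-WCCL is described as "measuring the frequency of DBT skills use (DBT Skills Subscale, 38 items"; a further 21 items measure dysfunctional coping. The success criteria are given in items. For the DBT-WCCL: "Intervention efficacy will be defined by a difference of at least 20% (i.e., 12/59 items) of improvement between groups after the intervention". For the CIB, success is "defined as at least 13% (i.e., 2/15 item) between groups after the intervention".

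Sample size {14} works with yes answers. For the CIB it assumes "a between-group difference by chance of 7% (i.e., 1/15 yes answers, where 15 is the total number of checklist items", rising to 13% (2/15). For the DBT-WCCL it assumes 7% (4/59) rising to 20% (12/59). Both sizes come from "applying a two-sided test for paired binomial proportions, with a significance level equal to 0.05 and a power of 0.8". They are 340 (170 per group) and 84 (42 per group), and the larger becomes 426 (213 per group) after 20% drop-out. In this section a fall in dysfunctional skills also counts as a yes on the DBT-WCCL.

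**The concern.** A category, such as rarely or sometimes used, belongs to one item. Neither the skills subscale nor the CIB has a category at scale level. The text does not say whether a student is improved when one item moves, when some number or share of items moves, or when a summary score moves, or how worsening items offset improving ones. Different readings classify different students as improved and can give different trial results.

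The thresholds and planning rates are in a different unit from the endpoint. The share of items on which answers improve is not the share of students who improve. Success could therefore be judged, and the sample size justified, on a quantity that is not the one compared between arms. Both primary outcomes, both success thresholds and the recruitment target rest on this definition. If the rule stays open, it could be chosen after the data are seen.

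**Working it through.** **Inputs (protocol article).** Two-sided alpha 0.05 (z = 1.96), power 0.80 (z = 0.8416), 1:1 allocation. CIB: 7% to 13% (1/15 to 2/15). DBT-WCCL: 7% to 20% (4/59 to 12/59). Functional items: 38 of 59.

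**1. Units and item sets.** The endpoint counts students, while the denominators 15 and 59 count items. Outcomes {12} scores functional skills only (38 items) but divides by 59. Twelve items are 12/59 = 20.3% of the whole checklist and 12/38 = 31.6% of the functional subscale; 20% of 38 is 7.6 items. Sample size {14} adds falls in dysfunctional skills, which Outcomes {12} does not.

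**2. Reproducing the stated sizes.** One-sample binomial formula: n = [(1.96·√(p0(1−p0)) + 0.8416·√(p1(1−p1))) / (p1−p0)]².

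- CIB: [(0.5001 + 0.2830)/0.06]² = 170.4 (stated: 170 per group).
- DBT-WCCL: [(0.5001 + 0.3366)/0.13]² = 41.4, rounded up to 42 (stated: 42 per group).
- Doubling gives 340 and 84. Then 170/0.8 = 212.5, rounded up to 213 per group, 426 in total.

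McNemar-type paired formulas with the two percentages as discordant proportions (two-sided) give 426–436 for the CIB and 118–125 for the DBT-WCCL. With exact fractions they give 344–353 and 108–116. No single choice of inputs to the paired formulas fitted both 340 and 84. The one-sample formula compares one group with a fixed rate, whereas the endpoint compares two arms.

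**3. The same percentages as student proportions in two independent arms.** n per arm = [(1.96·√(2p̄(1−p̄)) + 0.8416·√(p0(1−p0) + p1(1−p1))) / (p1−p0)]², with p̄ the mean of p0 and p1.

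- CIB, 7% vs 13%: [(0.8315 + 0.3553)/0.06]² = 391.3, so 392 per arm. Power with 170 per arm: Φ[(0.06·√170 − 0.8315)/0.4221] = Φ(−0.117) = 45%. With the unrounded 1/15 and 2/15 it is 54%.
- DBT-WCCL, 7% vs 20%: 108 per arm. Power is 41% with 42 per arm and 94% with 170 per arm.

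None of these figures allows for randomization by class.

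**4. The 13-point threshold as a difference in student proportions.** The article gives no expected proportion of improved control students. For assumed control proportions of 10%, 30%, 50% and 70%, a true 13-point difference with 170 per arm has power 90%, 70%, 68% and 81%. The planning figures do not say which applies.

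**5. Any-item reading (assumption: the planning percentages are per-item improvement probabilities).** With k independent items, P(improved) = 1 − (1−p)^k.

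- DBT-WCCL, k = 38: 1 − 0.93³⁸ = 93.7% vs 1 − 0.80³⁸ = 99.98%, a gap of 6.3 points.
- CIB, k = 15: 1 − 0.93¹⁵ = 66.3% vs 1 − 0.87¹⁵ = 87.6%, a gap of 21.3 points.

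With correlated items (beta-binomial, assumed correlation ρ):

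| ρ | DBT-WCCL, 7% vs 20% | CIB, 7% vs 13% |
|---|---|---|
| 0.1 | 66.4% vs 96.0% | 48.1% vs 71.2% |
| 0.2 | 50.4% vs 87.3% | 37.8% vs 59.2% |
| 0.3 | 39.8% vs 77.5% | 30.7% vs 50.0% |

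**The case against.** A reader might go further and infer that the endpoint saturates: nearly every control student improves on some item, so the 20-point DBT-WCCL threshold cannot be met. The documents do not support this, for four reasons.

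- The text never says that one item is enough. A summary-score reading or a count of items is equally open.
- The article calls 7% a chance difference between groups at baseline. Using it as a per-item improvement rate is an assumption.
- The ceiling needs nearly independent items. The article reports subscale alphas of .84 to .96. For 38 items, r = α/(38 − 37α) gives mean inter-item correlations of about .12 to .39. These refer to scores rather than changes, so they are only indicative. In the table above the DBT-WCCL gaps are 30 to 38 points, well over 20.
- The CIB does not saturate even with independent items: its 21-point gap exceeds the 13% threshold.

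It can also be said that an article condenses, and that an aggregation rule may stand in a fuller plan. That is fair for the missing rule alone. It does not rescue the thresholds and planning rates, which this document states in items and applies to a difference between proportions of students. Nor does it reconcile 38 with 59 items, or functional skills alone with functional plus dysfunctional skills.

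Lastly, 45% is not the trial's actual power. It follows from one reading of the percentages, and step 4 shows that other readings give lower or higher figures than 80%.

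**Conclusion.** The point holds as a mismatch between endpoint, thresholds and planning. Two parts need no assumption: no rule aggregates items to a student for either primary outcome, and the success thresholds and planning rates are item fractions used as student proportions. The conflicts over 38 versus 59 items and over dysfunctional skills are also plain in the text.

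The size depends on one reading. If 7% and 13% are student proportions in two independent arms, the CIB needs about 392 per arm rather than 170, and 170 gives about 45% power before clustering. On the same reading the DBT-WCCL needs 108 per arm rather than 42, which the larger CIB-driven sample covers before clustering. What can be said without choosing a reading is that the stated 80% power is not supported for the endpoint as written.

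A ceiling on the DBT-WCCL (94% vs 99.98%) is a conditional risk of the any-item reading with nearly independent items and 7% and 20% taken as per-item rates. It is not a property of the plan, and it does not extend to the CIB.

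**What to change.** Define response for each student as a stated change in the DBT Skills Subscale score (38 items) and in the CIB past-month total. Use the same item set in Outcomes {12} and Sample size {14}, and say whether dysfunctional skills count. Restate both thresholds and all planning rates as proportions of students, including the expected control proportion, and restate the power of the planned sample for a two-group comparison. Settle CIB scoring at the same time: the article describes a 5-point past-month scale but lists four categories.

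Baseline-adjusted mean subscale and total scores are an acceptable alternative. They need no responder cut-off, and the secondary outcomes already use mean scores. That route requires a target difference and power stated for those means.

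The cost is an amendment to the outcome definition of a registered trial whose recruitment began in November 2019, and probably a less favourable stated power. If means are used, the headline is no longer a percentage improved. No new data are needed. The definition should be fixed before anyone sees outcomes by arm.

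### The primary 'improved' rule does not say how many items must shift, and the Outcomes and Sample size sections count it in different units (students versus items) over different item sets (38 versus 59)

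*Protocol article*

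**What the plan says.** In the protocol article, Outcomes {12}, Emotional regulation skills, the primary comparison is "the proportion of participants categorized as “improved” post-intervention". The classification rule counts as improved "those participants with a difference of at least one category, toward improvement, from the baseline to post-intervention", applied to how often functional skills are used. The functional skills are the "DBT Skills Subscale, 38 items", and students rate "on a 4-point Likert scale, the frequency of use of each skill in the previous month". The success criterion follows: "Intervention efficacy will be defined by a difference of at least 20% (i.e., 12/59 items) of improvement between groups after the intervention".

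Under Impulsive behaviors the rule is parallel: "those participants with a difference of at least one category toward improvement from baseline to post-intervention in the frequency of impulsive behaviors". Success there is a 13% difference between groups, glossed as 2 of 15 items.

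Sample size {14} describes the same two outcomes as the pre/post change in the percentage of yes answers, where a yes is a one-category move in the better direction. Its examples are single-answer shifts. Its fractions are counted over items: 4/59 and 12/59 for the DBT-WCCL, 1/15 and 2/15 for the CIB. For the DBT-WCCL, a decrease on a dysfunctional item also counts as a yes.

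**The concern.** A student answers 38 functional items, each with its own four categories. To call that student improved by one category, the plan must say which item or items have to move, or how the 38 become one category. It says neither. The 12/59 gloss does not fill the gap, because it is attached to the between-group difference and not to the rule that classifies a student.

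Two things are at stake. If the student-level rule is applied literally and one item suffices, there are 38 chances to move up by ordinary answer variation. The control proportion may then sit so high that the declared success criterion cannot be met even by a programme that works. If instead the analyst chooses a reading later, the primary outcome can be settled after data have been seen.

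**Working it through.** **1. The plan's own figures.** 12/59 = 20.3%, 4/59 = 6.8%, 2/15 = 13.3% and 1/15 = 6.7%, so the stated 20%, 7%, 13% and 7% are all fractions of items. Outcomes applies the 20% and 13% to proportions of students. The item sets also disagree: 12 items is 20.3% of 59 but 12/38 = 31.6% of the functional items, and 20% of 38 is 7.6 items.

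**2. Readings side by side.**

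| Reading | Unit | Support in the text | Ceiling in controls? |
|---|---|---|---|
| Any one item moves | student | literal reading of Outcomes; not stated outright | yes, for many noise rates |
| Share of items that move | item | Sample size, and the 12/59 and 2/15 glosses | no |
| Minimum item count or scale-level category | student | none given | depends on the cut |

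**3. Any-one-item reading, DBT-WCCL, independent items.** Let p be the chance that a control student moves up on one item with no true change. The documents do not give p, so a range is shown. The proportion of controls improved is 1 − (1 − p)^38, and the room left for a difference is (1 − p)^38.

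| p | Controls improved | Room left |
|---|---|---|
| 2% | 54% | 46 points |
| 4% | 79% | 21 points |
| 5% | 86% | 14 points |
| 6.8% | 93% | 7 points |
| 10% | 98% | 2 points |

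Controls pass 80% when p exceeds 1 − 0.2^(1/38) = 4.15%. If upward and downward moves are equally likely, staying below that needs about 1 − 2 × 0.0415 = 92% of answers to be identical on two separate one-month recalls.

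**4. Same reading, correlated items.** Beta-binomial with within-student correlation ρ, a = p(1 − ρ)/ρ and b = (1 − p)(1 − ρ)/ρ; proportion improved = 1 − B(a, b + 38)/B(a, b).

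| p | ρ = 0.1 | ρ = 0.2 |
|---|---|---|
| 6.8% | 65% | 49% |
| 10% | 79% | 64% |
| 20% | 96% | 87% |

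The 80% line is crossed at p of about 10% (ρ = 0.1) or 16% (ρ = 0.2).

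**5. CIB, 15 items.** A simulation that assumed 80% to 90% 'never' answers per item and item test-retest correlation of 0.5 to 0.9 put 45% to 79% of controls as improved under the any-item rule. That leaves at least 100 − 79 = 21 points, so 13 is not blocked. An assumed true reduction of 0.3 SD gave differences of 1 to 11 points, which is compression under that chosen effect.

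**6. Would a replacement cut leave room?** With independent items and at least 12 of 38 required, control responders are about 0% at p = 10%, 6% at 20%, 22% at 25% and 48% at 30%, so a 20-point difference is possible. For a reliable-change cut at 1.96 on a normal scale score, with change SD √(2(1 − r)) and a true shift of 0.5 SD, the difference is Φ(0.5/√(2(1 − r)) − 1.96) − 0.025:

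- r = 0.84: 14.1% − 2.5% = 11.6 points
- r = 0.90: 20.0% − 2.5% = 17.5 points
- r = 0.96: 42.4% − 2.5% = 39.9 points

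The values 0.84 and 0.96 are the ends of the alpha range quoted under Outcomes, used here as a stand-in for reliability. Such a cut may itself miss 20 points.

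**The case against.** A reader might infer that nearly every control student will be improved on the skills scale and that the 20% criterion cannot be reached. The documents do not support that flat statement, for these reasons:

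- No sentence says that one item suffices. The 12/59 and 2/15 glosses and the Sample size section point to a share of items, and that outcome has no such ceiling.
- The 4/59 in Sample size is an assumed baseline difference between groups, not a per-item chance of improvement. Using 6.8% as a noise rate is only an illustration.
- At p = 2%, or at p = 6.8% with correlation of 0.1 to 0.2, controls stay at 49% to 65% and a 20-point difference remains arithmetically possible.
- For the CIB, a shortfall against 13 points depends on the effect size assumed.

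All of this stands, and it limits the conclusion to a conditional one.

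It can also be said that aggregation rules may sit in an analysis plan not shown, and that generalized mixed models of both outcomes over time are planned, so the responder count is not the only evidence. This carries less weight. The article does not merely leave the rule open. It states a student-level rule and success threshold in one section and an item-level outcome in another, over different item sets. The mixed-model sentence does not define 'improved'.

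**Conclusion.** The concern holds in conditional form. What rests on the text alone is that the primary responder rule has no item count or scale-level category, and that Outcomes and Sample size disagree on the unit (students versus items) and, for the DBT-WCCL, on the item set (38 functional versus 59). The primary result cannot be computed unambiguously from these sections.

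What rests on assumptions is the ceiling. If one item is enough, the 20-point difference is out of reach once per-item chance improvement exceeds about 4.1% with independent items, or about 10% to 16% with within-student correlation of 0.1 to 0.2. In that case an effective programme could be declared ineffective. For the CIB, only possible compression is shown.

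**What to change.** State one unit and one item set, identically in Emotional regulation skills, Impulsive behaviors and Sample size, and rule out an any-item definition. Two options:

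1. **Share of items per student.** The outcome is the proportion of items improved by at least one category (38 functional items for the DBT-WCCL, 15 for the CIB), compared between arms, with the 20% and 13% thresholds read on that scale. This is closest to the Sample size section. The item glosses need restating, because 20% of 38 is 7.6 items and not 12.
2. **A responder on the scale.** Define 'improved' by a cut on the subscale score, or by a minimum item count, fixed before unblinding. Restate the efficacy threshold to match, since a 1.96 reliable-change cut may give only about 12 to 18 points for a 0.5 SD shift at reliability 0.84 to 0.90.

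Under either option, rewrite the sample-size assumptions in the chosen unit. The cost is a protocol or analysis-plan wording change, plus a declared departure from the published definition and restated thresholds. No new data collection is needed.
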